### 2.2. Experimental manipulations

#### 2.2.1. Mood induction

The mood induction will last for about 15 min and will consist of asking participants to recall a difficult life event during which they experienced intense negative emotions (e.g., sadness, anxiety, or anger) and to write on paper the information regarding this event (e.g., age at the time of the event, place of the event, and individuals present during the event). Similar autobiographical mood inductions were used previously and were shown to be very effective (Baker and Guttfreund, 1993; Smith et al., 1997; Mayberg et al., 1999). For ethical considerations and to provide participants with a choice and a sense of agency and protect them from any negative effects, they will be informed in advance about the procedure, and provided with the choice to stop the experiment at any time (i.e., before, during, or after the mood induction, as well as before or during the discussion of the event with the other member of the dyad). They will also provide with a list of psychological resources if needed.

#### 2.2.2. Mindfulness training (MT)

In the absence of a validated protocol for interpersonal mindfulness in a general context, that is, outside parenting (Kabat-Zinn and Kabat-Zinn, 1997), couple (Carson et al., 2004), or counseling (Cohen and Miller, 2009), MBSR remains the most used and validated protocol for the general population (Khoury et al., 2015). MBSR is an 8-week, 2.5 h weekly session program that comprises different types of meditations (sitting, walking, eating) in addition to yoga, psychoeducation, group discussion, a half-day meditation retreat, and at home practices (40 to 45 min 6 days weekly). Therefore, MBSR requires participants to commit to 2.5 to 3 h each week and 45 min of mindfulness practice each day for 8 weeks. This can impact adherence to the program. In fact, adherence to standard MBSR is approximately 85% among highly motivated participants, whereas among a student population, the adherence rate falls to 70% (Williams et al., 2001). Taking that into consideration, we will implement a shortened version of MBSR, called MBSR-ld (light). In MBSR-ld, the duration of weekly meetings is reduced to 1 h, the daily practice is also reduced to 20 min (Klatt et al., 2009). Studies showed significant improvement in mindfulness disposition following MBSR-ld (Bergen-Cico et al., 2013), comparable effects of MBSR-ld to the original protocol (Klatt et al., 2009), and lack of support of the significant effects of the number of in-class hours on MBSR outcomes (Carmody and Baer, 2009). Similarly, in a recent RCT, low-dose mindfulness-based intervention led to significant increase in trait mindfulness, self-efficacy, body awareness, and reappraisal (Karing and Beelmann, 2021). Each group will include 6 to 8 participants. Sessions will be facilitated by two Doctoral trainees who received formal MBSR training. To ensure the quality of the delivery of the program the trainees will be supervised by a registered clinical psychologist, certified in MBSR.

#### 2.2.3. Relaxation training (RT)

The relaxation training (RT) is an active control, which is similar in structure and duration to MT. Sessions will be facilitated by 2 Doctorate level trainee counselors. Each session will include 1 h that integrates techniques of autogenic and progressive muscle relaxation, guided imagery, psychoeducation, and group discussion. Participants will be asked to practice these exercises at home for 20 min 6 days weekly using pre-recorded audio files. Similar protocols were used as a control group for mindfulness training (Jain et al., 2007).

### 2.3. Randomization and allocation concealment

A total of 640 participants will be randomly divided into four equal groups (of 160 each) using a computer-based algorithm administered by a third party to ensure concealment. One group will be designated as SPs while the other three will be designated as SRs. Thus, for each SP, three dyads with different SRs will be formed using a computer algorithm to ensure randomization, i.e., (SP, SR1) to assess the quality of the dyadic interaction pre-training, (SP, SR2), to assess the quality of the dyadic interaction post-training, and (SP, SR3) to assess the quality of the dyadic interaction at follow-up (total of 3 × 160 = 480 dyads; see Figure 2). The experimental design, allocation procedure, and analyses are intended to minimize the effects of the dyad (i.e., unique combination of SP/SR in a dyad) vs. the SP and SR effects on the measured outcomes. In addition, according to the power analysis using Monte Carlo simulation (Schoemann et al., 2014), which is appropriate for dyadic research (Ledermann et al., 2022), 80 dyads per group should be sufficient (powered enough) to detect moderate effects (i.e., changes between baseline, post, and follow-up time points), and thus, beyond the variability between the dyads (e.g., personalities and other personal/interpersonal characteristics).

**FIGURE 2 F2:**
[figure not shown]
Schematic representation of the randomization process.

### 2.4. Materials and measures

Sociodemographic characteristics of all participants (SP and SR) such as age, race, ethnicity, gender, occupation, and socioeconomic status will be measured using a sociodemographic questionnaire that will be developed for the study. The effects of the training on the SP will be assessed based on the S-ART framework using:

(1) Self-Awareness measures, including trait mindfulness using the Mindful Attention and Awareness Scale (MAAS; Brown and Ryan, 2003), with good reliability/validity (Osman et al., 2016) and Breath Counting Task (BCT) as a behavioral measurement of mindfulness (Levinson et al., 2014). We elected to use the MAAS as it directly measures self-awareness, which is a central element in the proposed model. In addition, the use of beath counting adds an objective behavioral measure to mindfulness and has been shown to be highly sensitive to mindfulness training (Isbel et al., 2020).

(2) Self-Regulation measures, including stress using Perceived Stress Scale (PSS; Cohen et al., 1983), good psychometric properties (Lee, 2012) and emotional regulation using Difficulties in Emotion Regulation Scales (DERS; Gratz and Roemer, 2004) and the Cognitive Emotional Regulation Questionnaire (CERQ; Garnefski et al., 2001). While the DERS focuses on regulation of negative feelings, the CERQ assesses cognitive strategies in emotional regulation, with both scales having shown strong psychometric properties (Garnefski and Kraaij, 2007; Kaufman et al., 2016).

(3) Self-Transcendence (prosocial) measures, including empathy and perspective taking using the Interpersonal Reactivity Index, (IRI; Davis, 1980), good psychometric properties (Davis, 1983), compassion for others using the Compassion Scale (CS; Pommier et al., 2020), and active listening using the Active-Empathic Listening Scale, (AELS; Bodie, 2011), which includes sensing, processing and responding.

In addition, the effects of the training on the SPs’ interpersonal mindfulness skills will be assessed using our recently developed and validated measure of interpersonal mindfulness, Interpersonal Mindfulness Questionnaire (IMQ; Khoury et al., 2022), which is based on Varela’s work (Varela et al., 1991, 2016) and the theory of embodiment (Khoury et al., 2017, 2019, 2020; Khoury, 2018) and include four sets of global trainable skills (detachment from automatic thoughts, body anchored presence, attention to and awareness of the other person, and empathic responding; Khoury et al., 2023). These skills were shown to highly relate to interpersonal functioning and were sensitive to meditation practice or mindfulness training (Khoury et al., 2022).

Daily logs will be used to measure adherence to and quality of home practice (during the 8-week training and the 3 months follow-up). In order to reduce the time for participants and increase feasibility, we will use the short forms (SF) of the scales when available (e.g., CERQ-SF; Garnefski and Kraaij, 2006; DERS-SF; Kaufman et al., 2016).

The effects of the training on the SP-SR interaction (O2.1/O2.2) will be assessed subjectively by the SRs using the Multidimensional Evaluation of Enacted Social Support (MEESS; Goldsmith et al., 2000), which includes three dimensions: *helpful*, *supportive*, and *sensitive* (Goldsmith and Fitch, 1997; Goldsmith et al., 2000; Goldsmith, 2016; Goldsmith and Griscom, 2017). While helpfulness focuses on providing assistance, or perspective (Dunkel-Schetter and Bennett, 1990; Goldsmith, 1992, 1994; Cutrona and Suhr, 1994), supportiveness refers to validation (non-judging or criticizing) (Winstead et al., 1992; Cutrona and Suhr, 1994) and sensitivity relates to the emotional support (Burleson, 1994; Burleson and Goldsmith, 1996). The scale is composed of 12 semantic items scaled on seven points and demonstrated high reliability and construct validity (Goldsmith et al., 2000). The MEESS was developed using student/community samples and has since been used in a variety of populations and situations (Goldsmith and Griscom, 2017), making it highly suitable for this study. To rate the quality of the dyadic interaction objectively, we will use the Behavioral Observational Measure of Dyadic Interactions (BOMDI; Cuperman and Ickes, 2009), which assesses verbal and non-verbal behaviors of the SP during their interaction with the SR. The BOMDI comprises seven verbal and nine non-verbal items. Verbal items include for example, the number of verbal acknowledgments displayed by the SP. Non-verbal items include for example, head nods, facial expressions, and eye contact. These measures assess the level of empathic listening and perspective taking of the SP during the interaction. Inter-rater reliability is high (Cuperman and Ickes, 2009). To ensure better reliability, two independent trained research assistants will code the dyadic interaction according to the BOMDI. Differences of two points or more between the raters will be discussed and if consensus is not reached, the primary investigator will be contacted.

As suggested by IER and SBT, attentive, empathic, and caring interpersonal interactions can help the SR to better self-regulate and such a regulation process is economic (i.e., requires less cognitive and emotional resources), therefore automatically triggered without the conscious awareness of the individual on the receiving end (Eisenberger et al., 2007). This is even more true following a negative emotional state, such as following the negative mood induction. SBT suggests that this process allows the support receiver (SR) to return to a baseline, which in our experimental paradigm, is a return to an emotional/mindful state similar to that before the mood induction. Therefore, the effects of mindfulness training of the SP on the SR (O3.1/O3.2) will be assessed using the Positive and Negative Affect Schedule (PANAS; Watson et al., 1988), which comprises 20 items, 10 measuring PA (e.g., excited, internal consistency = 0.89), and 10 NA (e.g., upset, internal consistency = 0.85). The PANAS was designed to measure affect in various contexts such as at present, and in the past, and demonstrated high construct validity (Crawford and Henry, 2004). Thus, it can be used to measure fluctuations in emotions (Tran, 2013), making it highly suitable for the current study. In addition, state mindfulness of the SR will be measured using the Mindful Attention Awareness Scale-State (MAAS-State; Brown and Ryan, 2003), which includes only five items and can be used in a non-meditative context, making it suitable to measure fluctuations in mindfulness state in the current context. To control for the response of SRs to the social support received from the SPs, we will use the Fears of Compassion from Others (FOCO; Gilbert et al., 2011). Finally, to control for Social Desirability we will use Marlowe-Crowne Social Desirability Scale (SDS; Crowne and Marlowe, 1960) for the SP and SR. Measures will be completed either using a paper-based format or on a tablet depending upon the preference of the participants. See Table 1 for a summary of the sequence of administering the measures. To film and record the dyadic (SP-SR) interactions, a high-definition 360-degree camera (1080P HD 360°Camera) with a built-in recording system will be used. The experiment will take place at the first author’s lab at McGill University.

**TABLE 1 T1:** Sequence of administering the measures during the experiment.

Outcome (variable)	Variable type	Dyadic interaction Part I, III and IV of the experiment				Mindfulness/Relaxation training Part II of the experiment			
		Pre-induction	Post-induction	During interaction	Post-interaction	Pre-training	During training	Post-training	3-months follow-up
Trait mindfulness	Dep/Cntrl					SP		SP	SP
Perceived stress	Dependent					SP		SP	SP
Emotional regulation	Dependent					SP		SP	SP
Empathy	Dependent					SP		SP	SP
Compassion–Others	Dependent					SP		SP	SP
Active listening	Dependent					SP		SP	SP
Perspective taking	Dependent					SP		SP	SP
Interpersonal mindfulness	Dependent					SP		SP	SP
Behavior observation	Dependent			SP-SR					
Enacted social Support	Dependent				SR				
Adherence to practice	Control						SP		
Emotional experience	Cntrl/Dep.	SR	SR		SR				
State mindfulness	Dependent	SR	SR		SR				
Fears of compassion	Control	SR							
Social desirability	Control	SR				SP			

Dep, dependent; Cntrl, control; SP, support provider; SR, support receiver.

### 2.5. Experimental procedure

#### 2.5.1. Experiment–Part I; pre-training

A total of 160 (SP, SR1) dyads will be invited to the lab. Upon arriving to the lab, members of each dyad will meet separately with two different research assistants (RAs). After signing a consent form, providing basic socio-demographic data, and filling-in the SDS, the SR will be asked to complete the FOCO (Gilbert et al., 2011), PANAS (Watson et al., 1988), and the MAAS-State (Brown and Ryan, 2003). Afterward, the SR will receive the 15-min mood induction while the SP will wait in a separate room doing an activity of their choice (e.g., reading popular magazines). Then, the SR will be asked to complete the PANAS and MAAS-State for a second time (as a check of the induction). Afterward, the SP and SR will be introduced to each other, the SR will be asked to discuss with the SP the event (which was part of the induction), and the SP will be asked to provide support to the SR as best they can during a 15-min videotaped interaction. The interaction will occur face-to-face, will be recoded, and the video will be rated by two trained graduate students according to the BOMDI (Cuperman and Ickes, 2009). Both the SP and SR will also be blind to the objectives of the study. Following the interaction, the SR will be asked again to complete the PANAS, MAAS-State, and the MEESS (Goldsmith et al., 2000). At the end of this part of the experiment, the SR will be debriefed about the study and its objectives.

#### 2.5.2. Experiment–Part II; mindfulness/relaxation training

SPs (total of 160) will be asked to complete measures of mindfulness, perceived stress, emotion regulation, empathy, compassion for others, active listening, perspective taking and interpersonal mindfulness. Then, they will be randomly and equally divided into two groups using a computer algorithm to ensure randomization and concealment. Half of the SPs (80) will receive the MT (MBSR-ld) and the other half will receive the RT. Participants in both groups will be asked to complete the daily logs during the 8 weeks. After the training, the same measures will be administered to the SPs.

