(Hbase) (a) At baseline, the S-ART measures of the SPs will be associated with the quality of SP-SR interactions (as measured objectively and subjectively) and with the emotional and mindful state of the SR and (b) the association between the S-ART of the SPs and the emotional/mindful states of the SR will be mediated by the quality of SP-SR interactions and moderated by Fears of Compassion from Others.

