#### 2.5.3. Experiment–Part III; post-training

This part will take place after the end of the training and is similar to Part I, the only difference is that SR1 will be replaced by SR2 in the dyads. In addition, only the SR will complete the consent form and provide socio-demo/social desirability data, as SPs already did that in Part I.

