#### 2.5.4. Experiment–Part IV; follow-up

This part takes place 3 months after the end of the training and is similar to Part III (with the only difference being that SR2 will be replaced by SR3 in the dyads). SPs will be asked to complete the same measures (mindfulness disposition, perceived stress, emotion regulation, empathy, compassion to others, active empathic listening, perspective taking, and interpersonal mindfulness skills). At the end of the experiment, both SPs and SRs will be debriefed about the study and its objectives.

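### By the order of the Parts, the support provider's S-ART measures follow the interaction at baseline but precede it at post-training, which leaves the directional reading of Hbase open to reverse causation

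*Protocol article*

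**What the plan says.** All places are in the protocol article.

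- **Baseline interaction (2.5.1, Part I).** While the support receiver (SR) undergoes the mood induction, "the SP will wait in a separate room doing an activity of their choice". The 15-minute interaction follows, and then the SR's outcomes: "Following the interaction, the SR will be asked again to complete the PANAS, MAAS-State, and the MEESS". No S-ART scale is listed for the SP in this Part.
- **Baseline S-ART (2.5.2, Part II).** The Part opens with "SPs (total of 160) will be asked to complete measures of mindfulness, perceived stress, emotion regulation, empathy, compassion for others, active listening", and randomisation to training comes next.
- **Post-training (2.5.2 and 2.5.3).** Part II ends with "After the training, the same measures will be administered to the SPs". Of Part III the article says "This part will take place after the end of the training and is similar to Part I", with a new SR.
- **Follow-up (2.5.4, Part IV).** The interaction is mentioned first. A separate sentence then says "SPs will be asked to complete the same measures (mindfulness disposition, perceived stress, emotion regulation". No word states which comes first.
- **Table 1.** The SP scales sit in a block of their own (pre-training, post-training, 3-month follow-up) that is not ordered against the interaction columns.
- **Use of the measures (1.3).** Hbase states: "At baseline, the S-ART measures of the SPs will be associated with the quality of SP-SR interactions". It extends this to the SR's state, with interaction quality as mediator. H2.2 makes the increase in S-ART the mediator of the training effect on interaction quality at post-training and at follow-up. Section 1.3 also describes baseline as preceding randomisation and the experimental procedure.

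**The concern.** Hbase gives S-ART the role of antecedent: it should explain how the interaction went and, through that, how the SR felt. Section 3 tests this with correlations and a bootstrap mediation macro. Neither can tell direction, so the main support for the directional reading is that the predictor was measured first. The baseline schedule, read in order, reverses this. Several S-ART scales are self-reports of empathy, compassion and active listening, which is what the SP has just attempted with a distressed stranger. A session that went well or badly could move those ratings and produce an association with quality even if the trait had no effect on it.

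The order also changes between baseline and post-training. Within-group S-ART change (H1.1(b)) then compares a score taken after an interaction with one taken before the next. The same baseline score enters the S-ART increase used in H2.2.

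**Working it through.** **Step 1: order of measurement.** The documents give no figure on this point, so the text is set side by side.

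| Time point | Order in the text | Basis |
|---|---|---|
| Baseline | interaction, then S-ART | Part I before Part II |
| Post-training | S-ART, then interaction | end of Part II before Part III |
| Follow-up | not fixed | two adjacent sentences in Part IV |

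Nothing in the article places S-ART before the first interaction. The wording of baseline in section 1.3, before the experimental procedure, fits poorly with scales taken after a support session.

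**Step 2: hypotheses touched.**
- Hbase: the predictor comes after the mediator and the outcome.
- H1.1(b): baseline and post-training scores are taken on different sides of an interaction.
- H2.2 at post-training: the post-training mediator score correctly precedes the outcome. The baseline score inside the increase follows an interaction.
- H2.2 at follow-up: undetermined.
- Mindfulness versus relaxation training: both arms follow the same sequence and baseline S-ART precedes randomisation to training, so this contrast is not biased.

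**Step 3: illustration of size for Hbase(a).** The number of baseline dyads, 160, and alpha 0.05 are from the article; a two-sided test is assumed. The rest is assumption: S-ART has no true effect on quality; the later self-rating moves by b SD per SD of the SP's impression of the session; and that impression correlates rho with quality as rated by the SR or the video coders.

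Spurious correlation: r = rho × b / √(1 + b²).

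Rejection probability by Fisher's z: with z = atanh(r) × √(160 − 3), it is 1 − Φ(1.96 − z) + Φ(−1.96 − z).

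Example, rho = 1 and b = 0.2: r = 0.2/√1.04 = 0.196; z = atanh(0.196) × √157 = 2.49; probability 0.70.

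| rho | b | r | z | Rejection |
|---|---|---|---|---|
| 1 | 0.1 | 0.100 | 1.25 | 24% |
| 1 | 0.2 | 0.196 | 2.49 | 70% |
| 1 | 0.3 | 0.287 | 3.71 | 96% |
| 0.5 | 0.1 | 0.050 | 0.62 | 10% |
| 0.5 | 0.2 | 0.098 | 1.23 | 23% |
| 0.5 | 0.3 | 0.144 | 1.81 | 44% |
| 0.3 | 0.1 | 0.030 | 0.37 | 7% |
| 0.3 | 0.2 | 0.059 | 0.74 | 11% |
| 0.3 | 0.3 | 0.086 | 1.08 | 19% |

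The rho = 1 rows are a ceiling for each b, because they equate the SP's own impression with quality as others rate it. The nominal rate is 5%.

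**The case against.** **The Parts may not be a strict timetable.** Table 1 files the SP's social desirability scale under the Part II pre-training column, while section 2.5.3 says SPs already completed it in Part I. The article may group the SP scales with the training for exposition. This stands as a caution: the baseline order is inferred from Part sequence, not from an explicit statement. It does not remove the point, because no text puts S-ART first, and the conflict itself needs resolving.

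**Follow-up.** A reader might infer from section 2.5.4 that the mediator is measured after the outcome in H2.2 at follow-up. The documents do not support that. Elsewhere the article uses sequence words where order is meant, and here there are none. All that can be said is that the order is open.

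**Size.** Most S-ART instruments are trait scales and one is a behavioural breath-counting task. Quality is rated by the SR and by coders, and nothing says the SP sees those ratings. This stands, and it is why the rows with rho below 1 matter.

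**Centrality.** Hbase is non-randomised and matches none of the numbered objectives, and part (a) claims only association. This stands and limits severity. Part (b), however, is a mediation claim and does rest on direction.

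**Priming.** Completing empathy and listening scales just before a support task may cue SPs who are meant to be blind to the objectives, and it is not shown that all the scales fit into the wait during a 15-minute induction. This stands against same-visit completion, but not against completing them earlier.

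**Conclusion.** The point holds in limited form. Read in the order of the Parts, S-ART follows the interaction at baseline and precedes it at post-training; at follow-up the order is not stated. The directional and mediation reading of Hbase is therefore open to reverse causation, and no later analysis of the baseline data can restore the missing temporal order. The change of order may also add an artefact to H1.1(b) and to the baseline component of the mediator in H2.2.

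The size is unknown. The rejection rates above depend wholly on the assumed shift and on the assumed link between the SP's impression and rated quality; neither is in the documents. A reader might take the schedule as a threat to the trial's main comparison. It is not, because the sequence is common to both arms and baseline S-ART precedes randomisation to training. This is a cheap improvement, not a flaw that undermines the trial.

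**What to change.** 1. State one order for all three time points, with the S-ART measures completed before the interaction. This is already the order at post-training.
2. Collect them preferably at enrolment, online or at an earlier visit, and not immediately before the task, to limit priming.
3. In the text, place baseline S-ART ahead of the Part I interaction and keep randomisation to training after it. In Part IV, say explicitly that the scales come first.
4. Align Table 1 with sections 2.5.1 to 2.5.4, and settle whether SPs complete the social desirability scale in Part I or in the Part II pre-training block.

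The cost is procedure wording plus an online or earlier completion. The sample size and the randomised comparison do not change. The small remaining downside is some priming, which would be the same in both arms and at all time points. For any cohort already past baseline, report the order actually used and describe Hbase as association without direction.

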## 2. Methods and design

### 2.1. Participants

We aim to recruit 640 adult community members (18–35 years old, 50% female) through advertising on social media. The sample size was based on detecting significant differences among the groups (i.e., between SPs with MT vs. SPs with RT), assuming a moderate effect (Khoury et al., 2013a,^2015^), a power of 0.8 and an alpha of 0.05 (Cohen, 1977) and the expectation 15 to 20% attrition rate. We will exclude participants who: (1) have a regular meditation practice; (2) have already participated in a formal mindfulness training (such as MBSR or a meditation retreat); or (3) had a social support skills training (e.g., counselors, psychologists, social workers, or other medical personnel).

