### 2.6. Timeline

The recruitment of participants will be divided into four cohorts (one cohort per year of 160, 40 SPs, and 120 SRs). The four parts of the experiment (i.e., Part-I, Part-II, Part-III, and Part-IV), will be repeated for each of the four cohorts. During each year (four in total), 40 SPs will be receiving training [MT(20), RT(20)]. The SPs receiving MBSR or RT will be divided into groups of 6 to 8 participants, and, a total of six groups will be conducted each year. We will conduct two groups (one MBSR, one RT) simultaneously during the fall, winter, and summer academic semesters of each year.

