## 3. Data analyses strategies

To ensure data reliability, self-reported data will be inspected for normality and skewness and outliers will be eliminated. Interrater reliability for the behavior observation data will be computed. An interrater coefficient of 0.95 or above is expected.

To test H1.1, H2.1, and H3.1, we will perform a mixed (2 groups × 3 time-points) multivariate analysis of covariance (MANCOVA) controlling for social desirability (and for Fears of Compassion from Others for H3.1). MANOVA/MANCOVA allow to reduce Type-I errors (i.e., rejecting the null-hypothesis when it is true, correcting therefore for multiple comparisons) when testing changes in multiple dependent variables. To test H1.2, we will use a regression analysis. To test H2.2 and H3.2, we will use a path analysis. To test associations and meditation/moderation at baseline (Hbase), we will use correlations and PROCESS macro with 5,000 bootstrapped/bias-corrected confidence intervals (Hayes, 2018). Structural Equation Modeling (Klem, 2000) may be used as well if the power is sufficient.

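### Training runs in 12 semester waves with both arms in each, but the allocation text does not say SPs are randomised within wave and the MANCOVA leaves wave out, which modestly overstates the standard error if waves differ.

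*Protocol article*

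**What the plan says.** All references are to the protocol article.

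- **Section 2.3:** "A total of 640 participants will be randomly divided into four equal groups", one of SPs and three of support receivers.
- **Section 2.5.2:** once the 160 SPs have filled in their pre-training measures, "they will be randomly and equally divided into two groups using a computer algorithm to ensure randomization and concealment". This puts 80 SPs in each arm. No block, stratum, cohort or semester is named.
- **Section 2.6:** recruitment runs in four yearly cohorts, and all four parts of the experiment, including the one that holds the training allocation, are repeated in each. Each year has 40 SPs, 20 MT and 20 RT, in training groups of 6 to 8. "We will conduct two groups (one MBSR, one RT) simultaneously during the fall, winter, and summer academic semesters of each year".
- **Section 3:** H1.1, H2.1 and H3.1 are tested with a mixed (2 groups × 3 time points) "multivariate analysis of covariance (MANCOVA) controlling for social desirability", plus Fears of Compassion from Others for H3.1. Wave, cohort and semester do not appear.
- **Section 1.3:** part (a) of H1.1 and of H2.1, and H3.1, are worded as differences between arms at post-training and at follow-up.

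**The concern.** The timetable in 2.6 puts both arms, in near-equal numbers, into every semester of every year. The design therefore takes differences between waves out of the arm contrast. A model with no wave term leaves those differences in its residual variance, so it reports a larger standard error than the design has earned.

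The allocation text does not say at what level SPs are randomised. Section 2.6 implies that it happens per cohort. How SPs reach a particular semester, and whether that is settled before the arm is drawn, is not stated. If arm is drawn by year and semester is assigned afterwards, placement in a wave is not itself protected by the randomisation.

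At stake is a small amount of power and a clear statement of the allocation procedure. Outcomes such as perceived stress could plausibly vary over the academic year, but the article gives no figure for this.

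**Working it through.** **Inputs from the article.** "a power of 0.8 and an alpha of 0.05" (two-sided assumed); "assuming a moderate effect" (no number given, d = 0.5 assumed); "the expectation 15 to 20% attrition rate"; 80 SPs per arm; 4 years × 3 semesters = 12 waves; 12 × 2 = 24 training groups; mean group size 80/12 = 6.7.

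**Assumed.** The share of outcome variance due to wave, ρ, taken as 0, 0.01, 0.05 and 0.10. The calculation treats one outcome at one time point.

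**Step 1: the plan's own figure.** A two-sample t-test at d = 0.5, two-sided alpha 0.05 and 80% power needs 64 per arm. With 20% attrition, 64/0.8 = 80 per arm. The stated 80 is reproduced.

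**Step 2: power with and without wave, balanced waves.** With wave in the model, the residual variance is 1 − ρ and df = 2n − 13. Without it, the planning calculation uses variance 1 and df = 2n − 2. Noncentrality is d / √(2(1 − ρ)/n), or d / √(2/n) without wave.

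| ρ | SE without wave too large by, 1/√(1−ρ) − 1 | n = 64: without → with | n = 80: without → with |
|---|---|---|---|
| 0 | 0% | 80.1% → 80.1% | 88.2% → 88.1% |
| 0.01 | 0.5% | 80.1% → 80.5% | 88.2% → 88.4% |
| 0.05 | 2.6% | 80.1% → 82.1% | 88.2% → 89.7% |
| 0.10 | 5.4% | 80.1% → 84.1% | 88.2% → 91.2% |

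**Step 3: the unadjusted test as it would behave with balanced waves.** Balance reduces the true variance of the estimate even when the model ignores wave. The unadjusted test therefore does slightly better than the 80.1% planning figure, and the realised gain is smaller than Step 2 suggests. By normal approximation at n = 64, the noncentrality is 0.5/√(2/64) = 2.83.

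- True alpha of the unadjusted test, P(|Z| > 1.96/√(1−ρ)): 4.4% at ρ = 0.05 and 3.9% at ρ = 0.10.
- Its power, Φ((2.83 − 1.96)/√(1−ρ)): about 81% and 82%.
- Power with wave, Φ(2.83/√(1−ρ) − 1.96): about 83% and 85%.

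**Step 4: simulation at 80 per arm (6,000 runs per setting).**

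- *Allocation by wave, ρ = 0.05, no treatment effect:* the SD of the estimated difference is 0.153 both with and without wave in the model. The estimate is equally precise; only the reported SE differs.
- *Type I error without wave:* about 4.1% at ρ = 0.05 and 4.2% at ρ = 0.10. The Monte Carlo SE is about √(0.05 × 0.95/6000) = 0.3 points, so this agrees with Step 3.
- *One overall split, for comparison:* SD without and with wave is 0.159 and 0.160 at ρ = 0.05, and 0.158 and 0.155 at ρ = 0.10. There is little difference.

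**Step 5: what a wave term does not do.** Now let the 24 training groups differ by an assumed intraclass correlation of 0.02, 0.05 or 0.10, with no wave effect. Type I error is about 6.9%, 8.5% and 11.5% without wave, and 7.0%, 8.9% and 12.1% with wave.

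**The case against.** **Allocation.** A reader might infer that 2.3 and 2.5.2 prescribe a single overall split that contradicts 2.6 or could not be run with rolling cohorts. The article does not support that. Section 2.6 repeats the part containing the randomisation in each cohort, and 4 × 20 = 80 per arm matches 2.5.2, so the figures there are study totals. A pre-generated list could also be filled as people enrol. Block detail is commonly left to a full protocol or analysis plan. What stands is narrower: randomisation within semester is implied by the paired groups but is stated nowhere.

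**Imbalance.** A reader might also infer that seasonal imbalance threatens the arm contrast. With one group of 6 to 8 per arm in every semester, entry counts within a wave can differ by at most about 8 against 6. Substantial imbalance by season is largely excluded.

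**Size.** The wave variance is assumed, and the unadjusted test still reaches about the planned 80%. Stable wave effects cancel from the group × time contrasts of a 2 × 3 model, leaving only wave × time variation. This is right for those contrasts. It does not cover the hypotheses worded as arm differences at post-training and at follow-up, from which wave effects do not cancel.

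**Model choice.** Adding a factor can be called a preference for the analysis plan to settle. However, the article names its covariates, and that list omits a factor its own timetable balances.

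**Conclusion.** The point holds as a minor improvement. The arms are balanced within 12 semester waves, the allocation text does not say SPs are randomised within wave, and the named covariates omit wave. If waves differ, the model's standard error for the between-arm comparisons is too large: by 0.5%, 2.6% and 5.4% at assumed wave shares of 1%, 5% and 10%. Against the 80.1% planning figure at 64 per arm, power with wave is 80.5%, 82.1% and 84.1%. Against the unadjusted test as it would behave with balanced waves, the gain is about 1 to 3 points at shares of 5% and 10%. At 0% nothing is gained and essentially nothing lost.

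Two stronger readings are not supported. The treatment estimate is not less precise or biased; with by-wave allocation its sampling SD is the same either way, and the cost is a conservative test. Nor can the trial's tests be called conservative overall. That direction applies to the wave effect taken alone, and clustering within training groups can push type I error above 5%.

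The figures rest on d = 0.5, two-sided testing, balanced waves, one outcome at one time point, and wave and clustering variances that the article does not give.

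**What to change.** 1. In 2.3 and 2.5.2, state that SPs are randomised 1:1 within each semester wave, in line with 2.6, and that an SP's semester is settled before the arm is drawn.
2. In section 3, add wave (12 levels), or at least cohort and semester, as a fixed factor in the H1.1, H2.1 and H3.1 models.

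The cost is an allocation list by wave, a sentence or two of text, and up to 11 degrees of freedom. At ρ = 0 and 64 per arm, power is 80.1% with or without the factor.

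This does not deal with clustering within the 24 training groups, which needs its own term alongside wave.
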